### Data Analysis Plan

#### Descriptive Statistics

Only cases with complete data will be used, with no imputations of missing values. We will summarize participant demographics (age, gender, specialty training area, and prior exposure to similar materials) for the entire sample and by order group (eg, whether the participant read first or listened first). We will report the mean and SD for all primary and secondary outcome measures (knowledge test scores, motivation, perceived learning, and cognitive load) by modality and article complexity.

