#### Sample Size Calculation

We conducted an a priori power analysis using G*Power (version 3.1; Heinrich Heine University) [21] for a mixed ANOVA with 1 within-subjects factor (learning modality: podcast vs reading) and 1 between-subjects factor (article-modality order). To detect a moderate effect size (f=0.25) for the main effects or interactions, with α=0.05 and power (1−β=0.80), the required total sample size is approximately N=44. To account for potential dropouts or missing data, we plan to recruit a total sample of N=60 resident physicians.

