#### Knowledge Tests

For each article, we developed a multiple-choice questionnaire to assess the comprehension and retention of key information. Each test consists of 10 questions in a single-best-answer format, and the sum of all correct answers represents the knowledge score. The questions cover important points from the article.

All questions were written specifically for this study. We ensured that each question could be answered based on the information in the article and that the AI podcast, if accurate, would also cover those points. We had 2 faculty members with a background in cardiology who were not involved in the study review the questions for content validity and clarity. Internal testing of the final items yielded no problems with comprehensibility.

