#### Motivation

To gauge participants’ motivation and engagement during the learning task, we will use items from the Intrinsic Motivation Inventory (IMI) [27], a well-established instrument for assessing subjective motivation in experimental tasks. We will focus on the interest and enjoyment as well as the effort and importance subscales of the IMI, as these are most relevant here. The interest and enjoyment scale serves as a measure of how enjoyable or engaging the student found the activity (considered a self-report proxy for intrinsic motivation), whereas effort and importance indicate how much effort they invested and how important they perceived doing well to be. Participants rate their agreement with the scales’ 7 (interest/enjoyment) and 6 (effort/importance) statements (eg, “I enjoyed doing this activity very much”; “I put a lot of effort into this”) on a 7-point Likert response from “strongly disagree” to “strongly agree.” The IMI has been used in educational studies and has shown good psychometric properties in various contexts (Cronbach α >0.80 in similar studies) [28], allowing the use of mean scores across all items of a scale as the final score.

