#### Primary Analysis

To assess the effect of learning modality and article complexity on comprehension, we will conduct a 2×2 mixed ANOVA with the following factors:

Within-subjects factor: modality (AI-generated podcast vs traditional reading)Within-subjects factor: article complexity (narrative case report vs technical research article)

Each participant completes both a reading task and a podcast task, 1 with the narrative article and the other with the technical article. The assignment of modality to article is counterbalanced. We will test for the main effects of modality and complexity, and their interaction, on knowledge test scores (range 0-10 per article). Effect sizes will be reported using eta squared (η²). Assumptions of normality (Shapiro-Wilk test on residuals) and homogeneity of variance (Levene test) will be examined. If assumption violations are detected, we will consider using robust ANOVA procedures [31].

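### The complete-data rule discards an observed knowledge score from anyone who finishes only one test, and it does not say whether completeness is judged per outcome

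*Protocol article*

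**What the plan says.** The missing-data rule is one sentence in the Data Analysis Plan, under Descriptive Statistics: "Only cases with complete data will be used, with no imputations of missing values". It refers to cases, does not define the term, and is not tied to any outcome. Primary Analysis and Secondary Analyses add no analysis set and no other missing-data rule.

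Each participant gives two primary scores: "Each participant completes both a reading task and a podcast task, 1 with the narrative article and the other with the technical article". These enter a single ANOVA with modality and article complexity as factors. The questionnaires are given after each task. Motivation has "7 (interest/enjoyment) and 6 (effort/importance) statements", Cognitive Load has 8 and Perceived Learning has 3.

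Sample Size Calculation expects some loss. It says that "the required total sample size is approximately N=44" and then: "To account for potential dropouts or missing data, we plan to recruit a total sample of N=60 resident physicians". Informed Consent lets participants withdraw at any time.

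**The concern.** Each participant supplies one score per modality and per article. A repeated-measures ANOVA on complete cases needs both, so a participant with one score is removed entirely (listwise deletion). The score already collected still carries information on both modality and article, and the rule discards it.

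Loss of the second test is plausible. Withdrawal is free, and the timed steps under Procedure add up to as much as 92 minutes, against a session of about 60 minutes in Inclusion Criteria. Whether someone stays for the second task could depend on which article and modality came first. Deletion could then be selective as well as wasteful.

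The second problem is the wording. A rule about cases, with no outcome named, can be read as requiring complete questionnaires before a participant's knowledge scores count. If that is not meant, the text should say so before data are seen. Otherwise the primary analysis set can be chosen afterwards.

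**Working it through.** **The plan's own figure.** Inputs from Sample Size Calculation: f = 0.25, α = 0.05, power 0.80, two measurements. For a within-participant effect the noncentrality is λ = f²·N·2/(1−ρ), where ρ is the correlation between a participant's two scores. The protocol gives no ρ. With two groups, N = 66 at ρ = 0, 46 at ρ = 0.3, 44 at ρ = 0.35 and 34 at ρ = 0.5. So 44 is matched for a within-participant effect with ρ about 0.30-0.35. The margin is 60 − 44 = 16, and 16/60 = 26.7%.

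**Session length.** Maximum times under Procedure: 5+30+5+5+2+30+5+5+5 = 92 minutes.

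**Value of a single test.** Assumptions: equal variances, correlation ρ, a participant random intercept, and single tests spread evenly over the four modality-article cells. Let P be the number of participants with both tests and s the number with one.
- Modality is estimated within participants. The information gained by keeping the single tests is (s/P)·(1−ρ)/2.
- Each participant sees two of the four cells, so the interaction is a contrast between the two assignment groups. The gain is (s/P)·(1+ρ)/2.

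| P | s | Modality, ρ = 0.2 / 0.35 / 0.5 | Interaction, ρ = 0.2 / 0.35 / 0.5 |
|---|---|---|---|
| 59 | 1 | 0.7% / 0.6% / 0.4% | 1.0% / 1.1% / 1.3% |
| 57 | 3 | 2.1% / 1.7% / 1.3% | 3.2% / 3.6% / 3.9% |
| 44 | 16 | 14.5% / 11.8% / 9.1% | 21.8% / 24.5% / 27.3% |

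Example: 16/44 × (1−0.2)/2 = 0.145, and 16/44 × (1+0.5)/2 = 0.273. Adding a period effect left these ratios unchanged when orders were balanced.

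**Questionnaire items, on the literal reading.** Items per task: 7+6+8+3 = 24, so 48 per participant. If each item is skipped independently with probability p (an assumption; the protocol gives no rate), the share losing complete status is 1−(1−p)^48:
- p = 0.2%: 9.2%, leaving 54.5 of 60
- p = 0.5%: 21.4%, leaving 47.2 of 60
- p = 1%: 38.3%, leaving 37.0 of 60

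The expected number falls below 44 once p exceeds 1−(44/60)^(1/48) = 0.64%. Secondary Analyses names only the interest and enjoyment part of the motivation inventory. If the 6 effort items are left out, the count is 2 × 18 = 36 and the shares are 7.0%, 16.5% and 30.4%. If completeness is judged per analysis, the loss to the knowledge analysis from these items is zero.

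**The case against.** The strongest reply is that the sentence sits under Descriptive Statistics, that knowledge scores are the only outcome of the primary ANOVA, and that each secondary outcome has its own ANOVA. Deleting incomplete cases within each analysis is then a natural reading, and a skipped motivation item costs the primary analysis nothing. This stands. A reader might infer that one blank item certainly removes a participant from the knowledge comparison, but the protocol does not say so. It leaves both readings open.

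The skip rates are assumed, and so is their independence. Skipping tends to cluster within people, which lowers the share affected at the same average rate. Supervised sessions at individual workstations may keep blanks rare. An unanswered knowledge question need not make a test incomplete, since "the sum of all correct answers represents the knowledge score" and a blank may simply score zero.

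A reader might also infer a power shortfall from missing data. The recruitment margin answers that for the modality test: at ρ = 0.3, power is 0.90 with 60 and 0.78 with 44. Nor is the margin a forecast of 16 participants with one test each. It also covers people who supply no test, whom no model recovers.

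On session length, 92 minutes is a ceiling. With the expected 12 minutes of listening and 15 of reading given under Learning Phase 1, the same steps sum to 5+12+5+5+2+15+5+5+5 = 59. Early departure is therefore possible, but the protocol does not make it likely.

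None of this touches the participant with one test. That score is lost on every reading.

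**Conclusion.** The point holds in a limited form. The complete-case rule is stated rather than merely left open, and it discards an observed primary score from anyone who finishes one test. It also fails to say whether questionnaire gaps affect the knowledge analysis.

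The size is unknown. A handful of such participants makes the gain small, and the upper figures need every one of the 16 spare participants to have exactly one test. The gain is larger for the interaction. The margin from 44 to 60 is also no protection there: with f = 0.25 on a between-participant contrast, the same method requires 66 participants at ρ = 0 and 98 at ρ = 0.5.

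Selective loss is plausible but unquantified. A reader might infer that the complete-case result will be biased, or that a mixed model would remove any bias. The protocol supports neither: it has no data on who leaves, and the mixed model helps only if missingness depends on what was observed (missing-at-random). The change is worth making because it costs almost nothing.

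**What to change.** Replace the sentence with three statements.

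1. Completeness is defined separately for each outcome, so gaps in a questionnaire do not remove a participant from the knowledge analysis.
2. The primary analysis uses every completed knowledge test in a linear mixed model with a participant random intercept and fixed effects for modality, article, their interaction and period. Missing-at-random is stated as its assumption.
3. The complete-case ANOVA is kept as a sensitivity analysis, with the number of participants who have one test reported by order and by modality of the first task.

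A rule for scoring partly answered scales would be useful but is optional detail. The cost is a few lines of wording and a standard model. No extra data are needed, and the Results section says that no one had been recruited when the protocol was submitted.

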#### Primary Analysis

To assess the effect of learning modality and article complexity on comprehension, we will conduct a 2×2 mixed ANOVA with the following factors:

Within-subjects factor: modality (AI-generated podcast vs traditional reading)Within-subjects factor: article complexity (narrative case report vs technical research article)

Each participant completes both a reading task and a podcast task, 1 with the narrative article and the other with the technical article. The assignment of modality to article is counterbalanced. We will test for the main effects of modality and complexity, and their interaction, on knowledge test scores (range 0-10 per article). Effect sizes will be reported using eta squared (η²). Assumptions of normality (Shapiro-Wilk test on residuals) and homogeneity of variance (Levene test) will be examined. If assumption violations are detected, we will consider using robust ANOVA procedures [31].

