### Study Design and Setting

We will conduct a single-center, 2-factor mixed experimental study with a 2×2 design. The within-subjects factor is the learning modality (AI-generated podcast vs traditional reading), and the between-subjects factor is the presentation order (ie, which article-modality combination comes first). Each participant will engage with 2 cardiology articles—1 practical case report and 1 technical research paper—experiencing 1 via reading and the other via an AI-generated podcast. The assignment of modality to article and the sequence of presentation will be fully counterbalanced across participants to control for order effects and content bias.

The study will take place at LMU Munich. Each participant will attend a single study session, during which they will read 1 article and listen to the other in podcast form. After each learning task, participants will complete a multiple-choice knowledge test and questionnaires assessing motivation, cognitive load, and perceived learning.

All study sessions will be conducted in a controlled classroom environment at LMU Munich. A researcher will be present throughout the study to supervise the session and ensure adherence to the protocol. The physical setting will be quiet, with individual desks and study materials provided on desktop computers or tablets. Participants in the podcast condition will be provided with noise-canceling headphones to standardize audio delivery.

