#### Orientation (5 Min)

Participants are welcomed and seated at a computer or tablet station. Written informed consent is obtained if not already collected during recruitment. Participants then complete a short intake form to gather demographic information (age, gender, and specialty area), confirm their participation in the Facharztprüfung preparation course, and verify their English proficiency and lack of prior exposure to the study materials. They are also screened for any sensory impairments that might interfere with reading or listening tasks.

Participants are randomly assigned to one of the counterbalanced order conditions (ie, whether they first read the narrative article or listen to the technical podcast, or vice versa). The researcher then provides access to the appropriate learning material.

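### The primary 2×2 ANOVA declares both factors within-subjects, but each resident fills only two of the four cells, so the stated model cannot test the modality × complexity interaction

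*Protocol article*

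**What the plan says.** The Primary Analysis section of the protocol article calls the model a 2×2 mixed ANOVA and gives it two factors: "Within-subjects factor: modality (AI-generated podcast vs traditional reading" and "Within-subjects factor: article complexity (narrative case report vs technical research article". No between-subjects factor is listed. The same section states the data layout, "Each participant completes both a reading task and a podcast task, 1 with the narrative article and the other with the technical article", adds that "The assignment of modality to article is counterbalanced", and names the tests: "We will test for the main effects of modality and complexity, and their interaction, on knowledge test scores". The Secondary Analyses section applies similar 2×2 mixed ANOVAs to the other outcomes.

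Other sections describe the structure differently. Study Design and Setting makes modality the within factor and says "the between-subjects factor is the presentation order (ie, which article-modality combination comes first". Sample Size Calculation also uses one within factor (modality) and one between factor (article–modality order). The Orientation step of the Procedure explains the randomised conditions as "whether they first read the narrative article or listen to the technical podcast, or vice versa", which names the two orders of a single pairing.

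**The concern.** A repeated-measures ANOVA with two crossed within-subjects factors needs all four cells from every participant. Here each participant has two, by design. The effect that cannot be recovered within a participant is the interaction, which is the hypothesis set out in the abstract's Objective and again in Textbox 1.

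The model cannot be run as written, so whoever analyses the data must choose an error term that the protocol does not name. Different choices give different P values for the interaction, and some also distort the modality test. The factor that carries the interaction, namely which article is read and which is heard, is not in the primary model at all.

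**Working it through.** **Layout.** Write R and P for reading and podcast, N and T for the narrative and technical article. Group A has cells RN and PT; group B has PN and RT. With 60 residents there are 30 per group and 120 scores.

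**Contrasts.**
- Interaction: (RN − PN) − (RT − PT) = (RN + PT) − (PN + RT). This is group A's total minus group B's total, so it is entirely between subjects.
- The within-person differences are RN − PT in group A, which carries modality plus article, and RT − PN in group B, which carries modality minus article. Their average gives the modality effect and half their difference gives the article effect. Both main effects are within-subject contrasts.

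**Estimability, simulated data set of 60 residents (30 per pairing).**
- Participant effects + modality + complexity: 62 columns, rank 62.
- Adding modality × complexity: 63 columns, rank 62. The interaction is aliased with participants.
- A repeated-measures routine given both factors as within-subjects stopped with a collinearity error.
- A random-intercept mixed model with the same three effects did fit. Its interaction statistic (|z| = 2.157) equalled the two-sample t on participant means (|t| = 2.157, 58 df), which confirms the between-subjects error term.

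**Cost of a wrong error term.** Let σ² be the variance of a score and ρ the correlation between a resident's two scores. The protocol gives no ρ; 0.5 is illustrative, with a range of 0.3 to 0.7. Per score, the between stratum has variance σ²(1+ρ) and the within stratum σ²(1−ρ); treating all scores as independent uses σ². By normal approximation, the actual type I error at nominal 5% is P(|Z| > 1.96/√ratio), where ratio is the true variance divided by the variance used.

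| Error term used | Effect tested | Ratio | ρ = 0.3 | ρ = 0.5 | ρ = 0.7 |
|---|---|---|---|---|---|
| All 120 scores independent | Interaction | 1+ρ | 8.6% | 11% | 13.3% |
| All 120 scores independent | Modality | 1−ρ | 1.9% | 0.6% | 0.03% |
| Within-subject error | Interaction | (1+ρ)/(1−ρ) | 15% | 26% | 41% |

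At ρ = 0.5, for example, 1.96/√1.5 = 1.60 gives 11%, and 1.96/√3 = 1.13 gives 26%. Simulation of the two interaction cases at ρ = 0.5 gave about 0.11 and 0.25.

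**The protocol's own N.** Sample Size Calculation gives about 44 for f = 0.25, α = 0.05 and power 0.80. With two groups and two measurements, the noncentrality for a within effect or a within × between interaction is f²·N·2/(1−ρ). The required N is 46 at ρ = 0.3, 44 at 0.35, 40 at 0.4 and 34 at 0.5. So 44 is reached with an unstated ρ near 0.35, and only for effects tested within subjects. For a between-subjects effect the noncentrality is f²·N·2/(1+ρ). At N = 60 and ρ = 0.5 this is 0.0625 × 120/1.5 = 5.0, giving 59% power (66% at ρ = 0.3, 54% at ρ = 0.7). Eighty per cent power would need 84, 98 and 110 residents at ρ = 0.3, 0.5 and 0.7.

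**The case against.** The strongest reply is that only the error structure is mislabelled. The three fixed effects named in the plan can all be estimated once participant is a random effect, and a competent analyst might do exactly that. This is true of the data, but the plan specifies an ANOVA with two within factors, and that is what fails. A primary analysis should not depend on its being silently replaced.

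Second, the between factor in Study Design and Setting, read as which of four article–modality combinations comes first, identifies all four sequences and hence the pairing. This reading is fair and narrows the conflict. Even so, the Primary Analysis section does not carry that factor forward, and Descriptive Statistics illustrates the order group merely as read first or listened first.

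Third, the Orientation wording is one loose parenthesis, against clear statements elsewhere that assignment is counterbalanced. Accepted: it needs aligning, because taken literally it would confound modality with article, but it does not show that such a design is intended. Nor does the rule "Only cases with complete data will be used, with no imputations of missing values" add to the case, since it most naturally means residents who finished both tasks.

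Fourth, the Introduction makes modality the primary objective and the interaction secondary, whereas the abstract puts the interaction first. The document is mixed on this, but the interaction is among the tests of the primary analysis on either reading.

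Finally, the error rates assume a particular analyst's choice and an unstated ρ. That also stands: they show what is at risk and do not predict what will be done.

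**Conclusion.** The concern holds. The two-within ANOVA in the Primary Analysis section cannot be fitted with its interaction, because each resident supplies two of four cells and the interaction is a comparison between pairing groups. This follows from the layout alone and needs no assumption about the data. The trial itself remains analysable, and both main effects remain within-subject contrasts.

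The size of the harm depends on the substitute chosen and on ρ. For ρ from 0.3 to 0.7, the interaction test runs at 8.6–13.3% if scores are treated as independent and at 15–41% if the within-subject error is used. Under independence the modality test becomes strongly conservative, which costs power and does not add false positives. With the correct error term, 60 residents give roughly 54–66% power for an interaction of f = 0.25. That is a consequence to acknowledge in the sample size text, not the basis of the finding. The specification must be corrected before analysis.

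**What to change.** Replace the model in Primary Analysis with one of these:

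- a mixed ANOVA with modality within and pairing (reads narrative vs reads technical) between, stating that the pairing main effect is the modality × complexity interaction and that modality × pairing is the complexity effect; or
- a linear mixed model with modality, article, modality × article and period as fixed effects and a random intercept for participant, fitted to all available scores.

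The two agree on the tests of the three effects when data are complete and period is left out. The period term and the use of all available scores are additions; using all available scores would require the complete-case rule in Descriptive Statistics to be amended.

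In either case, state that the interaction is tested between subjects on about N−2 degrees of freedom (58 with 60 residents).

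Name the four sequences, 15 residents each: read narrative then hear technical; hear technical then read narrative; hear narrative then read technical; read technical then hear narrative. Use the same factor names in Study Design and Setting, Sample Size Calculation, Orientation and Primary Analysis, and let Secondary Analyses follow. In the sample size text, state the assumed ρ and say which effects the N of 44 covers.

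The cost is wording only. The protocol reports no recruitment and no data at submission (August 2025); any correction made later should be dated and documented as a deviation, as the protocol already promises.

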## Discussion

### Anticipated Findings

This study evaluates AI-generated audio summaries (*AI podcasts*) as a tool for learning from scientific literature in postgraduate medical education. By directly comparing podcast-based learning with the traditional method of reading full-text articles, we aim to generate evidence on comprehension outcomes, learner motivation, cognitive load, and perceived learning. Because each participant will experience both modalities—reading and listening—our within-subjects design allows for more precise comparisons while controlling for individual differences in prior knowledge, attention, and learning preferences.

The findings will have practical implications for adapting learning materials for resident physicians preparing for board certification. If we find that reading leads to significantly better comprehension than listening, particularly for complex or technical content, this suggests that caution is warranted in using audio summaries as a standalone resource. Resident physicians may miss subtle but clinically important nuances when relying solely on AI-generated podcasts for learning. In such a case, AI-generated audio could still be valuable as a supplementary tool—useful for introducing new material, reinforcing key ideas, or supporting review during time-constrained situations such as commuting or night shifts. The results could also inform developers and content curators about the limitations of current AI summarization models, especially for dense scientific material, and point to areas where greater fidelity and detail are needed.

On the other hand, if comprehension is equivalent across modalities, even for technical articles, this would support the integration of AI-generated audio into formal and informal learning routines. AI podcasts could then be leveraged to increase the flexibility with which physicians access and absorb scientific information, without compromising accuracy or depth. Medical educators and institutions might consider systematically producing and offering AI-generated audio summaries of core readings or recent guideline updates, especially for busy clinicians with limited time for traditional study methods.

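### The primary model drops the order factor and has no period term, and its modality-by-complexity interaction is a between-person contrast that the within-subjects design does not protect

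*Protocol article*

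**What the plan says.** The protocol article describes the model in three places.

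- **Study Design and Setting** makes modality the within-subjects factor and presentation order the between-subjects factor. It says that the assignment of modality to article and "the sequence of presentation will be fully counterbalanced across participants to control for order effects and content bias".
- **Sample Size Calculation** powers a mixed ANOVA with modality within subjects and "1 between-subjects factor (article-modality order") between subjects. The target is stated as "To detect a moderate effect size (f=0.25) for the main effects or interactions", and the result is "with α=0.05 and power (1−β=0.80), the required total sample size is approximately N=44".
- **Primary Analysis** lists modality and article complexity, both as within-subjects factors, and continues: "We will test for the main effects of modality and complexity, and their interaction, on knowledge test scores". No order or period term appears. The secondary outcomes get similar models.

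The Orientation section randomises participants to the order conditions. In the analysis plan, order returns only as a grouping for the demographic summary under Descriptive Statistics.

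The intake form gathers "demographic information (age, gender, and specialty area"). English level is self-rated on four dimensions, and nothing below B2 is accepted. Neither variable enters a model.

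Anticipated Findings says that "our within-subjects design allows for more precise comparisons while controlling for individual differences in prior knowledge, attention, and learning preferences", with no exception for the interaction.

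**The concern.** The model to be fitted is not the one that was designed and powered. A factor that is randomised and used in the power analysis is missing from the primary model, and complexity is called within-subjects without noting what that implies when each person sees only one modality per article.

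The interaction is the hypothesis featured in the abstract's objective and the third hypothesis in Textbox 1. If it is a comparison between different people, pairing does not remove differences in ability, and its precision depends on how much people vary. The sample mixes internal medicine and cardiology trainees. The Articles section itself says that the echocardiography paper suits readers who already know cardiac imaging and valve disease. Specialty is therefore a plausible source of between-person variation, it is already recorded, and the model ignores it.

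Period is a separate matter. The protocol anticipates fatigue between tasks, since it offers a break to reduce it. A first-versus-second-task difference that is not modelled goes into the error term of the within-person tests.

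**Working it through.** **Inputs from the protocol:** f=0.25, α=0.05, required N=44, planned N=60, two scores per person. **Assumed, because not stated:** the correlation ρ between a person's two scores (0.5, range 0.3 to 0.7), the share R² of the variance of the person total explained by covariates, and the size of any period effect. Full counterbalancing of modality to article is taken from Study Design and Setting. The example in Orientation shows only one pairing; with that pairing alone the interaction could not be estimated.

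**1. The stated N.** For a within-person effect with two groups and two measures, the noncentrality is λ = f²·N·2/(1−ρ).
- At N=44 and ρ=0.35: λ = 0.0625·88/0.65 = 8.46 with 1 and 42 df, power 81%. This reproduces 44.
- At ρ=0.5 the same formula needs 34.
- For a between-person effect, λ = f²·N·2/(1+ρ), and 80% power needs 84, 98 or 110 participants at ρ = 0.3, 0.5 or 0.7.

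So 44 is a figure for a within-person effect.

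**2. What the interaction is.** Write RN, PN, RT and PT for read-narrative, podcast-narrative, read-technical and podcast-technical.

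Interaction = (RN − PN) − (RT − PT) = (RN + PT) − (PN + RT).

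One group of participants supplies RN and PT, the other PN and RT. The interaction is therefore the mean person total in one pairing group minus that in the other. With ±1 coding, the product of modality and complexity is the same for both tasks of a participant in all four counterbalanced sequences, so it varies only between people. The reading-versus-podcast comparison within either article is also between different people. The modality and complexity main effects are within-person contrasts.

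**3. Precision at N=60, ρ=0.5, in SD units.** With f=0.25 the two levels of an effect lie 0.5 SD apart.
- Modality: the variance of a within-person difference is 2(1−0.5)=1, SE = √(1/60)=0.129, and (0.5/0.129)² gives λ=15. Power is 97%.
- Interaction: the totals differ by 2·0.5=1.0, the variance of a total is 2(1+0.5)=3, SE = √(3·2/30)=0.447, and (1.0/0.447)² gives λ=5. Power is 59% (66% at ρ=0.3, 54% at ρ=0.7).

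**4. Covariates.** If they explain a share R² of the variance of the person total, λ = 5/(1−R²).

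| Assumed R² | λ | Interaction power, N=60 | N for 80% power |
|---|---|---|---|
| 0 | 5.00 | 59% | 98 |
| 10% | 5.56 | 64% | 88 |
| 20% | 6.25 | 69% | 78 |
| 30% | 7.14 | 75% | 68 |

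**5. Period.** An omitted difference of 0.5 SD between first and second task moves each person's reading-minus-podcast difference by +0.5 or −0.5, depending on order. This adds 0.25 to a variance of 1, a 25% inflation. Then λ = 15/1.25 = 12 and modality power is 93%; a simulation with 60 participants gave 94% without the term and 96% with it. For a period difference of 1 SD the simulated figures were 84% and 96%.

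**6. Validity.** In simulation under the null (4,000 runs), the type I error without covariates or period was 5.2% for the interaction and 4.8% for modality.

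**The case against.** The strongest reply is that nothing here is invalid. Randomisation and counterbalancing keep the unadjusted tests free of systematic bias, and the simulated error rates confirm it. That stands: a reader might infer a biased or invalid primary analysis, and the documents do not support that.

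Second, if the sample size section's order factor means the article-modality pairing, the primary model already contains it, because pairing is the interaction. That also stands. A reader might conclude that pairing must be added as a further term, but that would duplicate the interaction. What is absent is period and a correct label.

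Third, adjustment is a choice. English level serves as an eligibility screen and specialty as a descriptor, so they do have uses. The document gives no R². English is cut at B2 or above, and the Limitations section expects a shared internal medicine background to limit variation in prior knowledge. The gain may be nearer the 10% row or below it. Against this, the relevant knowledge for the technical article is cardiac imaging, on which the two specialties may differ.

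Fourth, it is tempting to argue from chance imbalance. A 20-point specialty imbalance combined with a 1 SD specialty gap would move the interaction contrast by 2·1·0.2=0.4 SD. That gap is assumed, and 0.4 is below one standard error (0.447). It is chance variation that the standard error already covers, not an added distortion.

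Finally, the sentence in Anticipated Findings opens by noting that each person experiences both modalities, so it is mainly about the modality comparison, for which it is right. The Introduction also makes modality the primary objective and the interaction secondary. Both points lower the stakes. They do not supply the missing caveat for the interaction.

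**Conclusion.** The point holds as one of consistency and precision. The design and sample size sections disagree with the primary model on the between-subjects factor, and the model has no period term. That the interaction is a between-person contrast follows from each participant supplying two of four cells and needs no assumption beyond the stated counterbalancing.

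The size rests on assumptions. At N=60, f=0.25 and ρ=0.5, interaction power is about 59% against about 97% for modality. That gap comes from the design and sample size, not from leaving out covariates; covariates would recover part of it, to about 64, 69 or 75% at R² of 10, 20 or 30%. The period term matters little unless the period effect is large: a few points of modality power at 0.5 SD.

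**What to change.** 1. Reconcile Study Design and Setting, Sample Size Calculation and Primary Analysis. Declare the article-modality pairing as the between-subjects factor that carries the interaction, test the interaction against between-person variance, and do not enter pairing as an additional term.
2. Add period (first or second task) to the primary and secondary models.
3. Prespecify specialty and self-rated English reading and listening level as fixed covariates in these models.
4. In Anticipated Findings, state that control for individual differences applies to the modality main effect and not to the interaction or the comparisons within one article.

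Stratifying the randomisation by specialty is optional.

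The cost is a change of wording and a few degrees of freedom. All variables are already collected, and the protocol reports no recruitment at submission. The gain from the covariates may be small, but fixing them now avoids choosing them after the data are seen.
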